**Figure 2: Flow-chart with timing of the assessments**

[figure not shown]

### 9.17 Sample preparation, storage, and shipment

All tubes and labels will be provided for each sample by the lab of the study-site. Each sample storage tube label should include protocol number, patient number, visit number and drug name. The date and actual clock time of each sample collection will be accurately recorded in the eCRF.

#### HIV-1 RNA, HCV-RNA, CD4 cells

- The blood samples will be stored for five years and then will be destroyed definitively.

#### Silibinin PK:

- Blood (6 ml) must be collected in ACD (acid citrate dextrose) solution vacutainer tubes. The tubes containing ACD solution should be stored at +4°C. Tubes must be identified with the patient ID number and sample number as soon as blood has been collected

- Blood samples must be brought to the laboratories without delay (maximum 30 min after blood collection).
- Treatment of samples: centrifugation at 1500g for 10 min at +4°C. In a class II biohazard hood plasma (obtained after centrifugation) should be divided in three labelled tubes (of approximately 1mL each) ready for freezing plasma at -80 °C, within one hour after collection. If this deadline cannot be met, please keep the sample at 4° C until centrifugation and freezing.
- The blood samples will be stored for 10 years and then will be destroyed definitively.

#### Drug level of antiretroviral drugs:

- Blood (10 ml) must be collected in EDTA solution vacutainer tubes. The tubes containing EDTA solution should be stored at +4°C. Tubes must be identified with the patient ID number and sample number as soon as blood has been collected
- Blood samples must be brought to the laboratories without delay (maximum 30 min after blood collection).
- Treatment of samples: centrifugation at 1500g for 10 min at +4°C. In a class II biohazard hood plasma (obtained after centrifugation) should be divided in three labelled tubes (of approximately 1mL each) ready for freezing plasma at -80 °C, within one hour after collection. If this deadline cannot be met, please keep the sample at 4° C until centrifugation and freezing.
- The blood samples will be stored for 10 years and then will be destroyed definitively.

#### Plasma aliquots:

- Two aliquots of EDTA plasma samples will be obtained at each study site on the screening visit, visit 1, 8, 12, 15. The aliquots will be used as backup-blood for potential later analysis. The aliquots should contain at least 5 mL plasma. The plasma samples will be stored at -20°C or colder.
- The plasma aliquots will be stored for 5 years in accordance to the biobank-protocol if a separate informed consent form was obtained.

#### PBMC's:

- PBMC's will only be obtained at the study site in Zurich
- One PBMC sample will be obtained on visit 1, 12 and 15. The PBMC sample should contain at least 10 mL heparin blood. The samples will be stored at -20°C or colder
- The PBMC's will be stored for 5 years in accordance to the biobank-protocol if a separate informed consent form was obtained.

The PK plasma and aliquots will be shipped to the central laboratory in Lausanne (laboratory [name]). Samples must be shipped with adequate dry ice in a suitable, durable shipment container to assure that samples remain frozen during transit. Enclose the inventory of samples with each shipment. The central lab will then check the PK samples to ensure the planned samples are accounted for and can be

properly identified. At the end of the study, one part of the stored plasma for PK-measures will be sent from the laboratory in Lausanne to RPH (Monza) RPH will also perform PK-determinations with its own developed assay. This procedure allows us to perform a “cross-over” validation of the different assays for drug-level measures.

The duration of sample storage will follow the respective SAMW Guideline regarding the collection of human biological material (Biobanking)

## 10 SAFETY

### 10.1 Definition of (Serious) Adverse Events

#### **Adverse events**

Adverse events (AEs) are defined as any untoward medical occurrence in a patient or clinical investigation subject administered a pharmaceutical product and which does not necessarily have a causal relationship with this treatment.

An AE can therefore be any unfavourable and unintended sign (including an abnormal laboratory finding), symptom, or disease temporally associated with the use of a medicinal study product, whether or not related to the medicinal study product. An AE may also consist of a new disease, an exacerbation of a pre-existing illness or condition, a recurrence of an intermittent illness or condition, a set of related signs or symptoms, or a single sign or symptom. The definition covers also medication errors and uses outside what is foreseen in the protocol, including misuse and abuse of the product, as well as events that could be associated with study procedures and which could modify the conduct of the trial.

AEs observed by the investigator and/or reported by the subject must be reported in the eCRF during the entire study period, i.e. the period of time from the first (= signature of informed consent) to the last protocol-specific procedure regardless of the medicinal study product relation assessment.

For all AEs, sufficient information will be pursued and/or obtained so as to permit an adequate determination of the outcome of the event (i.e., whether the event should be classified as an SAE) and an assessment of the casual relationship between the AE and the investigational drug or study treatment(s).

Whenever available, the underlying disease or condition for which a therapeutic or diagnostic procedure is required should be reported as the AE term. Surgeries or other invasive procedures that had already been planned prior to the start of the study do not have to be documented as AEs. These planned procedures will be recorded in the eCRF by the investigator at the baseline visit. It is not important if the condition was known before enrolment, only if the procedure was planned before.

Pregnancy per se does not classify as an AE. However, AEs related to a pregnancy have to be reported like any other AEs. Pregnancy should be confirmed by a reliable laboratory test. Pregnant subjects must be immediately withdrawn from the clinical study. All pregnancies occurring during the treatment phase of the study and within 30 days after discontinuation of study medication have to be reported to the Investigator-Sponsor within 24h of the investigational sites knowledge of the pregnancy on the Initial Pregnancy Report Form. The Sponsor-Investigator will contact the attendant physician by phone during pregnancy and after the estimated date of delivery to enquire about course and outcome of the pregnancy. Course of the pregnancy and health status of the new born child have to be documented on the Follow-Up Pregnancy Report Form.

#### **Serious adverse event**

An SAE is any untoward medical occurrence that at any dose results in

- results in death,
- is life-threatening,
- requires subject hospitalization or prolongation of current hospitalization,
- results in persistent or significant disability/incapacity, or
- is a congenital anomaly/birth defect,
- any important medical event and any event which, though not included in the above, may jeopardize the subject or may require intervention to prevent one of the outcomes listed above.

Any other medically important condition that may be not immediately life-threatening or results in death or hospitalization but may jeopardize the subject or may require intervention to prevent one of the outcomes listed above should also usually (i.e. based on medical and scientific judgment) be considered serious. For example: intensive treatment at home for allergic bronchospasm; certain laboratory abnormalities (e.g. blood dyscrasias); convulsions that do not result in hospitalisation; development of drug dependency or drug abuse.

#### **Suspected unexpected serious adverse reaction (SUSAR)**

A serious adverse reaction, the nature or severity of which is suspected to be not consistent with the applicable product information (current version of Legalon® SIL Investigator's Brochure, see section 10.6 for details).

#### **First Awareness Date (FAD)**

The first date any SPONSOR's employee or designee becomes aware of the minimum information for considering a case valid (i.e. (i) an identifiable patient, (ii) a suspect product, (iii) an identifiable reporting source, and (iv) an event). The clock for reporting purposes starts at the date of initial receipt (FAD) and it is defined as day 0.

#### **Adverse Drug Reactions (ADRs)**

"All untoward and unintended responses to an investigational medicinal product related to any dose administered".

### **10.2 Recording of (Serious) Adverse Events**

Clinical study subjects will be routinely questioned about AEs at study visits. The well-being of the subjects will be ascertained by neutral questioning ("How are you?"). The investigator is responsible for reporting all AEs occurring during the course of the study.

All observed or volunteered adverse drug events (serious or non-serious) and abnormal test findings, regardless of treatment group or suspected causal relationship to the investigational drug or study treatment(s) will be recorded in the patient file and subsequently in the eCRF.

AEs or abnormal test findings felt to be associated with the study treatment(s) will be followed until the event (or its sequelae) or the abnormal test finding resolves or stabilizes at a level acceptable to the investigator.

An abnormal test finding will be classified as an AE if one or more of the following criteria are met:

- The test finding is accompanied by clinical symptoms.
- The test finding necessitates additional diagnostic evaluation(s) or medical/surgical intervention; including significant additional concomitant drug treatment or other therapy  
**Note:** simply repeating a test finding, in the absence of any of the other listed criteria, does not constitute an AE.
- The test finding leads to a change in study dosing or discontinuation of subject participation in the clinical study.

All AEs, serious and non-serious, will be fully documented in the appropriate eCRF. For each AE, the investigator will provide the onset, duration, intensity, treatment required, outcome and action taken with the investigational product.

The intensity of AEs will be assessed as being

- mild (hardly noticeable, negligible impairment of well-being),
- moderate (marked discomfort, but tolerable without immediate relief), or
- severe (overwhelming discomfort, calling for immediate relief).

The investigator will determine the relationship of the investigational drug to all AEs as defined on the AE page of the eCRF.

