#### ***Primary endpoints:***

- Frequency of adverse events during iSIL treatment.
- Kinetics of the decline in HCV-RNA after 2 weeks of iSIL treatment (difference in IU/ml from day 1 to day 15, see flow-chart below).

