## **10.6 Potential risks/adverse events and treatment**

Due the limited size of the patient population with HCV treated with Legalon® SIL, the estimated incidence of possible adverse reactions provided below is based on the balance between the uncertainty of the actual proportions observed and the low absolute number of patients reporting the reaction, in comparison with the control group in controlled studies and taking into account the supposed relationship with treatment:

- Very common: sensation of heat.
- Common: diarrhoea, bilirubin increased, nausea, vomiting, headache.
- Uncommon: abdominal pain, fever, asthenia, shivering, feeling of body temperature change, abdominal discomfort.
- Rare: somnolence.

It should also be considered that the above incidences are not readily transferable to the general HCV patient population (probably with the exception of sensation of heat, diarrhoea and bilirubin increased), as most of the data on which they are based were derived from studies in special patient subgroups, often in critical conditions, such as patients in liver peri- or post-transplant situations.

Sensation of heat, feeling of body temperature change, shivering and fever usually occur during infusions at the beginning of treatment with Legalon® SIL and recede spontaneously on continuation of therapy. Slow infusions of Legalon® SIL might reduce their occurrence.

Bilirubin increase is a transient effect which spontaneously subsides upon Legalon® SIL discontinuation without treatment. Data collected so far indicate that bilirubin increase following Legalon® SIL administration is not accompanied by cholestatic or hepatotoxic effects.

No contra-indications are known other than hypersensitivity to the active substance or to the excipients. No interactions with other medicine or other forms of interaction are known.

The risk for clinically relevant metabolic drug interactions can be considered low based on in vitro studies and supported by clinical data collected in patients receiving Legalon® SIL and other concomitant medications who did not require any dose adjustments.

There are no adequate data from the use of Legalon® SIL in pregnant women and for this reason Legalon® SIL administration during pregnancy and lactation is not recommended.

There are no reported effects on ability to drive and use machines.  
No case of overdose has been reported.

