## 10.7 Assessment of safety laboratory parameters

The laboratory tests listed in Table below will be performed at the laboratory of each study site and the laboratory of [name] in Lausanne. For time points of laboratory sampling refer to the Flow Chart. Laboratory results of the patients will be available to the investigator of each study site and selected abnormal laboratory alerts will be sent automatically to the sponsor within 24 hours. Clinically relevant laboratory values should be commented on lab report print-outs. A clinically relevant value may be either in- or outside the reference range. Out-of-range data judged as clinically significant (CS) by the Investigator has to be report as an adverse event. Clinically relevant abnormal laboratory test results must be confirmed and should be repeated until normalization or stabilization or until an alternative explanation has been found.

| Category             | Test name                                                                                                                                                                                                                                                                                                               |
|----------------------|-------------------------------------------------------------------------------------------------------------------------------------------------------------------------------------------------------------------------------------------------------------------------------------------------------------------------|
| Haematology          | Hematocrit (Hct)
Hemoglobin (Hb)
Red Blood Cell Count/ Erythrocytes
White Blood Cells / Leukocytes
Platelet Count/ Thrombocytes
Diff. Automatic Neutrophils (relative count)
Eosinophils (relative count)
Basophils (relative count)
Monocytes (relative count)
Lymphocytes (relative count) |
| Coagulation          | Prothrombin time (Quick and INR)                                                                                                                                                                                                                                                                                        |

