## **12 STATISTICS**

### **12.1 Statistical and Analytical Plans**

The analyses of the primary and secondary endpoints of this non-comparative study will be purely descriptive. The average decline of HCV RNA during the lead-in phase (day +1 to day +15) will be expressed in  $\log_{10}$  IU/ml using methods for left-censored data (Tobit regression) (18) in case of undetectable values are encountered and represents the primary efficacy analysis and will be performed in the evaluable patients. We will further report the percentages (with 95% CI) of patients achieving undetectable levels of HCV RNA at the various time points. We will also attempt to analyse factors associated with  $\log_{10}$  HCV RNA response with mixed effects models (19) taking into account all measured HCV values from day -14 to day + 15. In these models, slopes will be allowed to change at day+1 and day +15. Potential co-factors will be first assessed in univariable and bivariable models to detect interactions and collinearities. Relevant effect modifiers and confounders will then be included in multivariable models. The following co-factors will be considered: age, gender, IL28B genotype, BMI, CD4 values and HIV RNA. We will look at the potential co-factors in univariable models first and only include relevant confounding variables in the multivariable analysis. Safety analyses will be performed including all patients that received at least one dose of the study medication (Safety Population). Adverse events will be reported in percentages (with 95% CI) of patients experiencing an event (for clinical events and abnormal laboratory values considered clinically significant by the Investigator – this represent the primary safety analyses) or the percentages below/above 1x and 2x normal range limits for laboratory values.

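### Adverse event intensity is defined only by discomfort, so an asymptomatic laboratory event fits only 'mild', and the laboratory tabulation stops at twice the normal limit with no link to day 1

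*Protocol*

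**What the plan says.** Section 10.2 requires the investigator to record an intensity for every AE, serious or not. The three levels are "mild (hardly noticeable, negligible impairment of well-being", "moderate (marked discomfort, but tolerable without immediate relief" and "severe (overwhelming discomfort, calling for immediate relief". There is no separate rule for laboratory events, and the protocol contains no grading by measured value.

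Laboratory findings become AEs by several routes, and not all of them need a symptom. Under section 10.2, accompanying symptoms are one criterion. Another is the need for further work-up or intervention, and a third reads "The test finding leads to a change in study dosing or discontinuation of subject participation in the clinical study". Section 10.7 adds: "Out-of-range data judged as clinically significant (CS) by the Investigator has to be report as an adverse event".

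Section 10.6 names a laboratory reaction among those expected: "Common: diarrhoea, bilirubin increased, nausea, vomiting, headache".

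For analysis, the primary safety endpoint in section 5.1 is "Frequency of adverse events during iSIL treatment". Section 12.1 reports the percentage of patients with an event, counting both clinical events and laboratory values that the investigator judges clinically significant. For laboratory values it also gives the "percentages below/above 1x and 2x normal range limits for laboratory values".

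**The concern.** The protocol creates a class of AEs, the asymptomatic laboratory events, and then asks for a grade on a scale that has no meaning for them. A patient whose infusions are stopped for an abnormal value, but who feels well, has an AE with negligible impairment of well-being, and the literal grade is mild. An investigator who finds that absurd has to improvise, and the grade may then differ between the seven sites.

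This trial is exposed to the problem. Safety is a primary aim, the patients have liver fibrosis, and raised bilirubin is an expected reaction. Severity also matters outside the tables: sections 10.1 and 10.4 classify a serious reaction as unexpected when its nature or severity departs from the Investigator's Brochure. Raised bilirubin is already an expected type of event, so severity is what would mark a particular case as unexpected. The only severity scale in the protocol is the discomfort scale, although the text does not formally tie the two together.

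**Working it through.** No figure in the protocol depends on the intensity scale, so there is nothing to recompute. The check is to follow an asymptomatic laboratory event through the text.

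**1. Is it an AE?** Yes, if it leads to work-up, intervention, a dosing change or discontinuation (10.2), or if the investigator judges it clinically significant (10.7). No symptom is needed.

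**2. Which intensity does it get?** Moderate needs marked discomfort and severe needs overwhelming discomfort. An event with neither fits only mild. The measured value does not enter the definition.

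**3. Does section 12.1 recover the size?** Only in part. For an upper limit U the cut-offs are U and 2U. Taking illustrative values:

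| Illustrative value | 10.2 intensity if asymptomatic | 12.1 class |
|---|---|---|
| just above 2U | mild | above 2x |
| 5U | mild | above 2x |
| 10U | mild | above 2x |

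A value of 10U is 10/2 = 5 times the highest cut-off, yet it shares both its grade and its class with a value just above that cut-off.

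**4. Does section 12.1 use the day 1 value?** It does not mention it. Three illustrative patients:

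| Day 1 | Worst on treatment | Ratio to day 1 | 12.1 class on treatment |
|---|---|---|---|
| 5U | 5U | 5/5 = 1 | above 2x |
| 5U | 10U | 10/5 = 2 | above 2x |
| 1U | 5U | 5/1 = 5 | above 2x |

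No change, a doubling and a fivefold rise all look the same. The eligibility criteria in sections 7.1 and 7.2 require fibrosis and set no limit on bilirubin, transaminases or platelets, so patients may enter with abnormal values. The protocol does not say how many will.

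**5. What about decreases?** For a lower limit L, twice the limit is 2L, which is greater than L. A value below 2L need not be low at all. The 2x cut-off therefore has no clear meaning for platelets, haemoglobin, neutrophils or albumin.

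**6. Is there another scale?** Section 10.5 refers to an alert limit and section 10.7 to laboratory alerts, but the protocol gives no numeric value for either.

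**7. Are the data there?** Yes. The study schedule has safety laboratory tests on days 1, 2, 4, 8, 12 and 15.

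**The case against.** The strongest reply is that little is lost. Clinically significant laboratory values enter the primary safety analysis whatever their intensity. Section 12.1 also tabulates laboratory values by size. Section 10.1 allows certain laboratory abnormalities to be serious AEs. Section 10.2 records treatment required, outcome and action taken, and section 7.4 has the reason for discontinuation documented. All of this stands. A reader might infer from the scale that a severe laboratory toxicity could not show up in the results at all; these routes show that it could.

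A reader might also infer that the report will state a count of zero severe laboratory events. The protocol plans no table by intensity, so that too is not supported.

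It is also fair to say that the protocol never calls asymptomatic laboratory events mild. It is possible to read it as not having considered them, and laboratory events that come with symptoms can be graded as written.

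Finally, shift tables and further cut-offs are often left to a statistical analysis plan, and the raw values allow any grading to be derived later. This carries weight for the display, but not for the intensity rule. That rule is an instruction which investigators follow when they complete the case report form, it is stated without exception, and an analysis plan does not change what they enter. The 1x and 2x cut-offs are likewise fixed in the protocol text.

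**Conclusion.** The point holds as a defect in severity recording and laboratory reporting. On a literal reading, an asymptomatic laboratory AE is graded mild at any value. The section 12.1 tabulation does not separate values above 2x the limit, and it does not separate drug effect from abnormality present on day 1.

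The size is limited. The primary AE frequency would be the same under any intensity scale, and large abnormalities stay visible as clinically significant AEs, in the class above 2x, or as serious AEs. How many patients would be misgraded cannot be estimated, because the protocol gives no expected distribution of laboratory values.

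The conclusion assumes that investigators apply section 10.2 as written and that no other study document gives them a laboratory grading. It is a cheap improvement and does not threaten the main result.

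**What to change.** In section 10.2, restrict the discomfort scale to clinical (symptomatic) events. State that laboratory AEs are graded by measured value with a pre-specified grading table for each analyte, extending above 2x the upper limit and treating decreases separately.

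In section 12.1, add each patient's worst on-treatment laboratory grade and the shift from day 1. Replace the 2x cut-off for decreases with the grades of that table.

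The cost is an amendment to two sections and to the AE guidance for sites, and slightly more analysis work. No extra sampling and no change to treatment is needed. The severity table may look less favourable than one based on discomfort.
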